Previous studies evaluating the use of the biportal endoscopic technique in LSS surgery have reported good clinical results; however, the strength of evidence has been limited by the use of a retrospective study design and small sample sizes [10, 11]. There is currently a lack of level 1 studies to establish the efficacy and stability of the biportal endoscopic technique in comparison with conventional methods. Therefore, we aim to compare the efficacy and safety of biportal endoscopic decompressive laminectomy with those of conventional decompressive laminectomy in a multicenter, prospective randomized controlled trial (RCT). Our hypothesis is that the efficacy and safety of these two methods are similar in patients with LSS.

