##### Radiographic outcomes

The degree of central canal release and canal dimension, as measured using postoperative magnetic resonance imaging (MRI) or computed tomographyOther radiographic complications, as assessed using simple radiographs during the follow-up period

Baseline radiographs in the anteroposterior, lateral, flexion, and extension views will be used to score spondylolisthesis and segmental instability at the surgery level. A preoperative spine MRI will be systematically checked, and the severity of the canal compromise will be evaluated based on Schizas classification [16].

Safety will be assessed by evaluating all adverse and severe adverse events; all incidents will be reported to the appropriate institution, as required. All outcomes will be recorded by the blinded assessor in the eCRF system (Table 1).

**Table 1 Tab1:** Evaluation schedule

Visit type	Screening	Operation	Follow-up			
Visit	1	2	3	4	5	6
Visit week	-4–0 weeks	0–2 days	2 weeks	12 weeks	24 weeks	52 weeks
			± 5 days	± 4 weeks	± 8 weeks	± 8 weeks
Informed consent	O					
Demographics^a^	O					
Inclusion/exclusion	O					
Randomization		O				
Operation		O				
MRI (or CT)^b^	O	O				
Simple radiographs	O		O	O	O	O
ODI	O		O	O	O	O
EuroQol 5-dimensions	O		O	O	O	O
VAS	O		O	O	O	O
POSAS				O	O	O
Other surveys^c^			O	O	O	O
Adverse events		O	O	O	O	O

*MRI* magnetic resonance imaging; *CT* computed tomography; *ODI* Oswestry Disability Index; *VAS* visual analog scale for low back pain and radiating pain of the lower extremities; *POSAS* Patient and Observer Scar Assessment Scale

^a^Baseline patient characteristics, including past medical/surgical history, physical examination, and laboratory tests

^b^A CT scan will be obtained if MRI cannot be performed

^c^ Including surgery satisfaction, walking time, and postoperative return to daily life period

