#### Sample size and statistical analysis

This trial will recruit 120 participants (60 participants per group) to confirm the primary outcome equivalence between biportal endoscopic and conventional decompressive laminectomy. Previous studies have indicated a minimal clinically important ODI difference of 12.8 [17], as well as a standard deviation of 18.8, at 1 year after endoscopic decompressive laminectomy [18]. A required sample size of 60 patients per group was determined based on these values and the following parameters: alpha of .05, power of .90, two-sided confidence interval of 95%, and a 20% loss to follow-up.

All statistical analyses will be performed using SPSS 26.0 (version 26.0, Chicago, IL, USA). A *P* value < .05 will be considered significant. A modified intention-to-treat (mITT) analysis will be used. The mITT strategy indicates that participants are analyzed on whether they underwent a randomly assigned surgery (to avoid the effects of crossover and dropout, which may disrupt the random assignment to the treatment groups). Participants who do not complete the follow-up schedule will be excluded from the analysis, and there will be no additional enrollment.

In each group, changes in secondary outcomes from baseline to follow-up will be analyzed with repeated measures analysis of variance. Differences in other clinical and radiologic outcomes, as well as adverse events, between the two groups will be analyzed using Student’s t-test (for continuous variables) and chi-square test (for categorical variables).

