## Discussion

The aim of this multicenter, prospective RCT is to compare the efficacy and safety of biportal endoscopic decompressive laminectomy with those of conventional microscopic decompressive laminectomy in patients with LSS. While endoscopic spine surgery, in particular, the biportal endoscopic technique, has become an increasingly used approach in this patient group, it is not without certain challenges.

Previous studies have suggested that a sufficient level of experience is essential for performing biportal endoscopic surgery in patients with lumbar stenosis. Biportal endoscopic decompressive laminectomy has a particularly steep learning curve, as competency in this technique requires the completion of approximately 58 cases [19]. Indeed, a previous study reported that complications occurred in 7 (10.3%) of 68 cases during this learning curve [20]. Therefore, under the premise that conventional spine surgery requires skill, a learning curve of approximately 60 cases is considered necessary for the biportal endoscopic technique.

Nevertheless, previous studies have indicated that the clinical outcomes achieved with the biportal endoscopic technique are similar to those of open microscopic surgery when the learning curve is completed; the biportal endoscopic technique has also been shown to yield superior early postoperative outcomes [10, 18, 21]. According to a recent meta-analysis of 383 patients from five studies, the majority of postoperative clinical outcomes are equivalent between biportal endoscopic laminectomy and conventional microscopic laminectomy [11]. However, the biportal endoscopic technique has been shown to have additional advantages, such as less immediate postoperative back pain, a shorter length of hospital stay, earlier ambulation, a reduced need for opioids, and lower postoperative segmental instability [21–23].

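### As written, the exclusion of non-completers also applies to the adverse-event comparison, which can understate harm; a non-significant chi-square at this size would not show similar safety

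*Protocol article*

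**What the plan says.** Under Sample size and statistical analysis, the article names one analysis approach: "A modified intention-to-treat (mITT) analysis will be used". It explains that "participants are analyzed on whether they underwent a randomly assigned surgery (to avoid the effects of crossover and dropout", and then adds: "Participants who do not complete the follow-up schedule will be excluded from the analysis". The rest of that sentence says that no further patients will be enrolled.

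The following paragraph of the same section covers safety. Differences in other outcomes, "as well as adverse events, between the two groups will be analyzed using Student’s t-test (for continuous variables) and chi-square test (for categorical variables". The general threshold is that a P "value < .05 will be considered significant". No analysis set is named for adverse events, and no margin or interval for safety is given.

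Elsewhere:

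- Radiographic outcomes: "Safety will be assessed by evaluating all adverse and severe adverse events". Table 1 collects adverse events from the operation visit through week 52.
- Background: "Our hypothesis is that the efficacy and safety of these two methods are similar in patients with LSS". The abstract's Discussion repeats the hypothesis of comparable efficacy and safety.
- Abstract, Methods: the modified intention-to-treat (mITT) method is mentioned for the primary outcome only.

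**The concern.** Whether a patient finishes 12 months of follow-up can depend on the harm being measured. Someone who dies, or withdraws after a dural tear, a reoperation or a poor result, is a non-completer because of the event. Removing that patient removes the event from the numerator. If one operation causes more events of this kind, its rate is lowered more and the contrast between arms shrinks.

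The stake is one of the trial's two stated hypotheses. Similar safety is put beside similar efficacy, and the article expects its results to inform practice guidelines. Yet the only between-group safety analysis described is a test of difference, in a trial whose size was set without reference to safety.

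**Working it through.** **1. What the text fixes.**

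| Place | Statement | Limited to efficacy? |
|---|---|---|
| Abstract, Methods | mITT for the primary outcome | Yes, but it concerns mITT and does not mention the non-completer exclusion |
| Statistical section, 2nd paragraph | mITT will be used; non-completers are excluded | No |
| Statistical section, 3rd paragraph | Adverse events compared by t-test or chi-square | Safety is included, with no exception |
| Radiographic outcomes and Table 1 | All adverse events evaluated, from the operation on | Not applicable |

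Events are thus collected in patients whom the statistical section then removes from the analysis.

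**2. The plan's own sample size.** Inputs from the statistical section: ODI difference 12.8, SD 18.8, two-sided alpha 0.05, power 0.90, 20% loss.

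n = 2 × [18.8 × (1.960 + 1.282) / 12.8]² ≈ 45.3, so 46 per arm. Then 46 / 0.80 = 57.5, so 58, close to the stated 60.

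The ODI inputs alone account for the size; no safety input enters. (Whether this formula suits the equivalence aim is a separate question.) At the planned loss, 0.20 × 60 = 12 patients per arm leave and 48 remain.

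**3. How exclusion can change the result (hypothetical counts).**

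- One arm: 6/60 = 10.0%. If two patients with events are the only losses, 4/58 = 6.9%.
- Two arms, everyone counted: 12/60 (20.0%) against 4/60 (6.7%), a difference of 13.3 points; uncorrected chi-square 4.62, P = 0.032.
- Same data after 12 losses per arm, where the first arm's losses include 4 of its 12 events and the second arm's include none: 8/48 (16.7%) against 4/48 (8.3%), a difference of 8.3 points; chi-square 1.52, P = 0.217.
- If loss were unrelated to events, the expected counts would be 12 × 0.8 = 9.6 and 4 × 0.8 = 3.2 of 48. The rates would stay at 20.0% and 6.7%, with no bias.

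**4. What the adverse-event comparison can show.** The article gives no expected event rate for either arm. Its only figure of this kind is from an earlier biportal series in the Discussion: "complications occurred in 7 (10.3%) of 68 cases during this learning curve" (7/68 = 0.103). I assume 10% for scale only.

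95% half-width for the risk difference with 10% in both arms, 1.96 × √(2 × 0.10 × 0.90 / n):

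- n = 60: 1.96 × √0.00300 = 0.107
- n = 48: 1.96 × √0.00375 = 0.120

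Power of the uncorrected chi-square for 10% against 20%, by full binomial enumeration: 0.326 at 60 per arm and 0.293 at 48. With assumed rates of 5% against 10%, power is about 17% at either size.

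The observed contrast can also be large without reaching significance: at 48 per arm, 12/48 (25.0%) against 5/48 (10.4%) gives P = 0.061.

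**5. Separating the two issues.** Keeping all 60 per arm raises power only from 29.3% to 32.6% and narrows the half-width only from 12.0 to 10.7 points. Retaining the patients removes selective loss. It does not cure the low precision, which comes from the trial's size.

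**The case against.** The strongest reply is that the exclusion was meant for efficacy. The abstract ties mITT to the primary outcome, the exclusion sentence ends with a remark about not replacing losses, and the ODI sample size allows for those losses. A safety population is commonly defined in a full protocol or analysis plan, and neither is shown here. This is plausible as intent, but the point does not rest on a missing safety set. It rests on a printed rule with no limit to efficacy, in the section that also analyses adverse events. A later safety set would have to override that rule.

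Three parts of the reply stand, and each rules out a stronger reading:

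- **Crossovers and conversions.** A reader might infer that they are dropped from the safety comparison as well. The mITT sentence can be read that way, but an as-treated reading is possible and the article never mentions conversion to open surgery. Their handling is unclear.
- **Non-significance read as similarity.** A reader might infer that the plan will treat P > .05 as proof of similar safety. The article does not say so, and its sized confirmatory claim is ODI equivalence. It does state a similar-safety hypothesis and describes no other between-group safety analysis.
- **The 10% rate.** It is not this trial's planning rate. It comes from a learning-curve series of one technique, and applying it to both arms is an assumption.

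It is also fair that evaluating all events and analysing a subset are different activities. Events in early leavers would still be recorded and reported to institutions. They would nonetheless be absent from the comparison on which a safety statement would rest.

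**Conclusion.** The point holds in limited form. Read as written, the non-completer exclusion reaches the adverse-event comparison and is at odds with the commitment to evaluate all adverse events. It can understate harm if leaving follow-up is related to events; that direction is expected, not certain, and loss unrelated to events would cause no bias. The size of any bias cannot be derived from the article. The counts above only show that a loss at the planned 20% could move a hypothetical comparison from P = 0.032 to P = 0.217, and they assume that all the lost events fall in one arm.

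Separately, and whichever analysis set is used, the trial cannot establish similar safety through a non-significant chi-square. Under the illustrative 10% rate the interval is about ±11 to ±12 points, and about two in three true doublings to 20% would go undetected. The ODI analysis is not affected by this point.

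**What to change.** In Sample size and statistical analysis:

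1. State that the exclusion of non-completers does not apply to safety.
2. Analyse adverse events in all patients who had a study operation, with every event up to last contact. Tabulate by operation received and also by randomised arm, so that any crossover or conversion stays visible whichever way the mITT sentence is meant.
3. Report the between-group risk difference with a 95% confidence interval, using exact methods where events are sparse.
4. Present safety as estimated with its interval, not as shown to be comparable, and adjust the hypothesis wording in the Background and the abstract to match. State that a non-significant test will not be taken as evidence of similar safety.

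The cost is some wording and one extra table, with no added patients or visits. The downside is a more modest safety conclusion. The change removes selective loss but leaves precision limited: under the illustrative rate the interval would still be about ±10.7 points with all 60 per arm.

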## Abstract

**Background:**

Recent studies on biportal endoscopic spine surgery in patients with lumbar spinal stenosis have reported good clinical results. However, these studies have been limited by the small sample sizes and use of a retrospective study design. Therefore, we aim to compare the efficacy and safety of biportal endoscopic decompressive laminectomy with those of conventional decompressive laminectomy in a multicenter, prospective, randomized controlled trial.

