#### Secondary outcomes

##### Clinical outcomes

Visual analog scale (VAS) score for low back pain and radiating pain of the lower extremities: scores range from 0 to 10; a higher score indicates more severe painPatient’s quality of life, as assessed by the EuroQol 5-dimensions questionnaire (EQ-5D): EQ-5D contains five questions with five responses for each question, and the total score is converted into the final EQ-5D value, ranging from 0.000 to 1.000; higher score indicates a better quality of life [15].Surgery satisfactionWalking timePostoperative return to daily life periodSurgical scars, as evaluated using the Patient and Observer Scar Assessment Scale 2.0, which contains six parameters with 10-point scoring system; 6 represents normal skin and 60 represents the worst scar imaginableSurgery-related variables, such as postoperative drainage (mL), operation time (minutes), admission duration (hours), and postoperative creatine kinase (International Unit/L)

Patient-reported outcomes will be collected from the participants at baseline and at 2 weeks, 3 months, 6 months, and 12 months after surgery.

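### As worded, back pain, leg pain and EQ-5D are tested only for change within each arm, so the plan states no comparison of the arms for them

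*Protocol article*

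**What the plan says.** Two consecutive sentences in Sample size and statistical analysis set the methods. The first reads: "In each group, changes in secondary outcomes from baseline to follow-up will be analyzed with repeated measures analysis of variance". It names no group factor and no group-by-time term. The second reads: "Differences in other clinical and radiologic outcomes, as well as adverse events, between the two groups will be analyzed", by Student's t-test for continuous variables and the chi-square test for categorical ones.

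The Background gives the purpose as a comparison: "we aim to compare the efficacy and safety of biportal endoscopic decompressive laminectomy with those of conventional decompressive laminectomy". The hypothesis there is also comparative: "Our hypothesis is that the efficacy and safety of these two methods are similar in patients with LSS".

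On timing, the Clinical outcomes section states: "Patient-reported outcomes will be collected from the participants at baseline and at 2 weeks, 3 months, 6 months, and 12 months after surgery". Table 1 (Evaluation schedule) is narrower. Among the listed secondary clinical outcomes, only VAS (back and leg) and EQ-5D are marked both at screening and at all four follow-up visits. The scar scale has no screening mark. Neither has the row for other surveys, whose footnote reads: "Including surgery satisfaction, walking time, and postoperative return to daily life period".

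**The concern.** A repeated measures ANOVA run separately in each arm asks whether that arm's mean changes over time. It makes no use of the randomised contrast. Patients in both arms are having decompression and can be expected to improve, so the likely output is two significant results that say nothing about whether one technique is better, worse or similar. Where the change is small, one arm may cross P < .05 while the other does not, and a reader may take that as a difference.

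What is at stake is the comparative reading of pain and quality of life. The Discussion cites lower immediate postoperative back pain as an advantage of the biportal technique, so early VAS back pain is a likely subject of a claim. As worded, the plan gives it no between-group estimate. Two significant within-arm results could equally be presented as support for similarity, which they are not.

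**Working it through.** **Which outcomes are affected.** Table 1 and the Clinical outcomes section, set against the two sentences:

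- VAS back, VAS leg, EQ-5D: baseline and four follow-up visits. They fit the first sentence (change from baseline, in each group).
- Scar scale, satisfaction, walking time, return to daily life: no screening mark. Without a scheduled baseline they fit the second sentence (between groups).
- Drainage, operation time, admission duration, creatine kinase: perioperative. They also fit the second sentence.

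The word *other* in the second sentence separates its outcomes from those just assigned to the within-arm analysis. The gap is therefore clear for three outcomes.

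**The plan's own figure.** No sample size or power is stated for secondary outcomes. The stated 60 per group concerns the primary outcome. With ODI difference 12.8, SD 18.8, two-sided alpha 0.05 and power 0.90, n = 2 × (1.960 + 1.282)² × (18.8/12.8)² = 45.3, so 46. Allowing for 20% loss, 46/0.80 = 57.5, so 58, close to 60. The only number used below is the completers per arm: 60 × 0.80 = 48.

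**Illustration of what the within-arm test can show.** From the documents: 48 per arm and five time points. Assumed, because the documents give nothing for these outcomes:

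- normal data with equal correlation 0.5 between visits;
- improvement e (in SD units) reached in the proportions 0, 0.6, 0.9, 1, 1 over the five time points;
- an arm difference of 12.8/18.8 = 0.68 SD, borrowed from the ODI.

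*Within-arm test.* F has 4 and 4 × 47 = 188 degrees of freedom, with noncentrality λ = n × e² × Σ(p − p̄)² / (1 − ρ). Here p̄ = 0.7 and Σ(p − p̄)² = 0.49 + 0.01 + 0.04 + 0.09 + 0.09 = 0.72, so λ = 48 × 0.72/0.5 × e² = 69.12 e².

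- e = 1.5: λ = 155.5, power 1.00.
- e = 1.5 − 0.68 = 0.82: λ = 46.4, power above 0.999.
- e = 0.35: λ = 8.47, power 0.62. Exactly one arm significant: 2 × 0.62 × 0.38 = 0.47.
- e = 0.25: λ = 4.32, power 0.34. Exactly one arm significant: 2 × 0.34 × 0.66 = 0.45.

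*Between-group test of change at 12 months.* The SD of the change is √(2 × (1 − 0.5)) = 1, so the standard error is √(2/48) = 0.204. For a true difference of 0.68, z = 0.681/0.204 = 3.34, and power = Φ(3.34 − 1.96) = 0.92.

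**Simulation with the same inputs (4,000 runs per case).**

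| True state | Both arms significant | Exactly one significant | Between-group t-test | Group-by-time test |
|---|---|---|---|---|
| Both improve 1.5 SD | 100% | 0% | 5.0% | 4.7% |
| 1.5 v 0.82 SD | 100% | 0% | 91.3% | 90.8% |
| Both improve 0.35 SD | 39.3% | 46.5% | 4.6% | 4.9% |
| Both improve 0.25 SD | 12.0% | 44.6% | 5.0% | 5.0% |

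The first two rows give identical within-arm results, although the arms are equal in one and differ by 0.68 SD in the other. In the last two rows the arms are equal, yet the within-arm tests disagree in nearly half the runs.

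**The case against.** The best defence is one of reading. *Other* clinical outcomes could mean clinical outcomes other than the primary one, which would give VAS and EQ-5D a between-group t-test after all. The authors may also have intended a two-factor ANOVA with group as the between-subject factor. The article condenses a fuller protocol, and an analysis plan may exist. These readings are possible, but the first sentence says the analysis is done in each group and names no interaction. The sentence is a stated method, not a detail left out, and if something else was meant the wording still needs correcting.

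Other parts of the defence stand, and they limit the point. A reader might infer the following, and the documents do not support it:

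- *That the plan has no between-group test for secondary outcomes, or that all of them are affected.* The second sentence supplies such tests. The outcomes without a baseline mark in Table 1 can reasonably be read as covered by it. The Clinical outcomes sentence on baseline collection is looser than the table.
- *That spurious differences are the expected result.* Disagreement between the arms is frequent only when within-arm power is moderate. If both arms improve substantially, it is close to zero, and the harm is that the result is uninformative.
- *That repeated measures ANOVA will lose many patients through missed visits.* The same section already excludes participants who do not complete the follow-up schedule, so such a loss cannot be pinned on the ANOVA.
- *That failing to adjust for baseline is a fault of the within-arm test.* Baseline is already a level of the time factor, and within one arm there is no treatment contrast for a covariate to sharpen.

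**Conclusion.** The point holds for VAS back pain, VAS leg pain and EQ-5D. As worded, their change from baseline has only a within-arm test, which cannot address the aim of comparing the techniques or the hypothesis that they are similar. The conclusion follows from the type of test and does not depend on any number.

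The illustrative size rests on the assumed correlation, recovery profile and effect sizes: at large improvement the within-arm results are the same whether the arms are equal or differ by 0.68 SD, and at 0.25 to 0.35 SD exactly one arm is significant in about 45% of runs with no true difference. The documents do not say which case applies to any outcome.

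These are secondary outcomes with no power claimed, and the primary outcome is not touched. The change should be made, but the point does not threaten the trial's main result.

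**What to change.** For VAS back, VAS leg and EQ-5D, replace the within-group ANOVA with one between-group longitudinal model per outcome: group, visit, group-by-visit and baseline value, for example a mixed model, which the stated software can fit. Report the between-group difference with its 95% CI at each of the four follow-up visits. Keep changes within each arm as description, without using their P values to compare the arms. State explicitly which outcomes fall under the t-test and chi-square sentence, so that *other* is no longer open to two readings.

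The cost is a change of wording and slightly more analysis work, with no extra data or patients. A hospital term is optional and not needed for this repair. Whether patients with incomplete follow-up should be analysed is a separate question: it would change the stated analysis population and needs its own decision.
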